#### Economic analysis

The economic evaluation will take the form of an incremental cost-utility analysis taken from the societal perspective over a 6 month pre intervention vs 6 month post intervention time-horizon. This analysis will estimate the cost per quality adjusted life year gained from providing the Senior Exercise Park intervention and supervised exercise program (incorporating the optional continuation of the supervised program). Change in quality adjusted life year will be modelled using data from EQ-5D-5 L utility instrument scores collected at baseline, and 12 month assessments. Hospitalisations measured using participant self-report of diagnosis and days spent in hospital will be converted to a cost using the National Weighted Activity Unit funding approach (https://www.ihpa.gov.au/what-we-do/national-weighted-activity-unit-nwau-calculators). Productivity in paid and unpaid labour will be calculated using responses to the iMTA questionnaire [33]. Change in community service use, home nursing, allied health will be valued using market rates for comparable services provided through the private sector.

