**Table 1 Tab1:**
[figure not shown]
ENJOY study procedure

Abbreviated Mental Test Score (AMTS), a set of 10 questions to assess cognitive impairment (memory), will be administered on the initial assessment [14]. Participants who score < 7/10 will be excluded from the study. Participants will then be asked to complete the Exercise and Sport Science Australia (ESSA) exercise screening tool to evaluate any contraindicated medical conditions to exercise: https://www.essa.org.au/wp-content/uploads/2011/09/Screen-tool-version-v1.1.pdf. Participants answering ‘yes’ to any of the screening questions will be required to obtain medical clearance from their general practitioner prior to participation in the exercise intervention.

At baseline, 3 months and 9 months participants will undergo a comprehensive suite of physical (strength, balance, functional mobility) tests, falls risk assessment and falls history, and complete psychosocial (quality of life, enjoyment, social isolation, fear of falls, loneliness), and mental health measures (mental wellbeing, depression). In addition, they will be asked to provide feedback and complete satisfaction surveys (survey 1 and 2). Health cost/services data will also be collected (health economic evaluation). At 12 months, a final assessment will take place (via phone and or mail postage) to evaluate health cost/services as part of the health economic data collection. Monthly falls calendars will be collected from baseline for 12 months.

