##### Psychosocial, mental and quality of life health outcomes

Psychosocial, mental health and quality of life outcomes will be assessed using the following questionnaires:(i)Health-related quality of life will be assessed using the EQ-5D-5 L [20]. The EQ-5D-5 L is a generic instrument to assess health related quality of life that comprises five dimensions (mobility, self-care, usual activities, pain/discomfort and anxiety/depression) as well as overall utility score.(ii)*Mental wellbeing* will be assessed using the five-item World Health Organisation (WHO-5) Wellbeing questionnaire [21, 22]. The WHO-5 measures psychological wellbeing and depressive symptoms using 5 simple questions with adequate validity both as a screening tool for depression and as an outcome measure in clinical trials [23].(iii)*Loneliness* will be assessed using the UCLA 3-Item Loneliness Scale. The UCLA Loneliness Scale includes three dimensions of loneliness: relational connectedness, social connectedness and self-perceived isolation [24, 25].(iv)*Depression* will be assessed using the short version Geriatric Depression Scale (GDS-15) [26]. The GDS (15 point version) is a valid depression assessment tool specifically designed for older people.(v)*Fear of falls* will be assessed using The Short Falls Efficacy Scale International (Short FES-I) questionnaire [27]. The Short FES-I is a valid and reliable 7 items scale to assess fear of falling in older people.(vi)*Self-efficacy* barriers to exercise will be assessed using The Self-Efficacy for Exercise (SEE), a 9-item instrument that focuses on self-efficacy expectations related to the ability to continue exercising in the face of barriers to exercise [28].(vii)
*Enjoyment* will be assessed using the 8 item version Physical Activity Enjoyment Scale (PACES) [29]. The PACES is a valid instrument for assessing enjoyment in physical activity.(viii)
*Social isolation and social support* will be assessed using the short version 6 items Lubben Social Network Scale [30]. The Lubben Social Network Scale is a self-report valid and reliable measure of social engagement including family and friends.

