##### Health care resource use and productivity

Health care costs will be measured using Medicare and Pharmaceutical Benefits Scheme database extractions for publicly subsidized primary health services. Hospitalisations will be measured using participant self-report of diagnosis and days spent in hospital. Productivity costs will be measured using the iMTA Productivity Cost Questionnaire [33] which includes three modules measuring productivity losses of paid work due to 1) absenteeism and 2) presenteeism and 3) productivity losses related to unpaid work. Participants will be asked to complete this questionnaire at baseline and 12 month follow up assessments. Home nursing, allied health and community service use will be captured using self-report. For the 12 month assessment, the form will be posted to the participants in addition to the EQ-5D-5 L. A reply paid envelope will be enclosed so participants can post these directly to the research team.

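### The cost-utility horizon (6 months before versus 6 months after the intervention) is undated and not reconciled with QALYs taken from baseline and 12 months, and the 3- and 9-month EQ-5D-5L readings are not used for QALYs

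*Protocol article*

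**What the plan says.** The Economic analysis section describes an incremental cost-utility analysis from the societal perspective "over a 6 month pre intervention vs 6 month post intervention time-horizon". The horizon is given to the analysis as a whole, and no start or end date is attached to either half. The object of evaluation is the park intervention and the supervised program, with the optional supervised continuation included. The QALY change is to be modelled from "EQ-5D-5 L utility instrument scores collected at baseline, and 12 month assessments".

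The data available are wider than that. The Procedure section says "At baseline, 3 months and 9 months participants will undergo a comprehensive suite of physical" tests and will "complete psychosocial (quality of life, enjoyment, social isolation, fear of falls, loneliness), and mental health measures". The section on psychosocial, mental and quality of life outcomes names the instrument: "Health-related quality of life will be assessed using the EQ-5D-5 L". The section on health care resource use and productivity adds a posted EQ-5D-5L at 12 months. EQ-5D-5L is therefore available at 0, 3, 9 and 12 months.

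On costs, the Procedure section says of the baseline, 3- and 9-month visits that "Health cost/services data will also be collected (health economic evaluation"), with a further collection at 12 months. For the productivity questionnaire, "Participants will be asked to complete this questionnaire at baseline and 12 month follow up assessments".

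**The concern.** A cost per QALY can be interpreted only if costs and health gain refer to the same stated period and that period contains the intervention being valued. Here the horizon is two half-years, while the utility points are a full year apart. The term post intervention is open as well, because the structured program ends at about month 3 and the unstructured phase, with its optional supervised sessions, ends at about month 9. If the window is chosen once data are in hand, several defensible choices could give quite different ratios.

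The second issue stands apart from the first. Supervision stops at 3 months and continuation is optional, so there is little reason to expect utility to move in a straight line from baseline to month 12. A model that sees only the two ends cannot register a gain that peaks and fades, or one that arrives late. The Discussion says councils need evidence to decide on wider installation of such parks, and the cost per QALY would bear on that decision.

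**Working it through.** The economic section reports no computed figure, so there is nothing to reproduce. The check has two parts.

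**1. Post window against the schedule.** Inputs, all from the protocol article: the structured program runs from month 0 to about month 3 and the unstructured phase to about month 9 (Design and setting); EQ-5D-5L is at 0, 3, 9 and 12 months; productivity is at 0 and 12 months; the QALY model uses 0 and 12 months.

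| Post window | Fit with the stated utility points |
|---|---|
| Months 0–6 | No assessment at month 6; the 12-month reading lies outside; the 3-month reading inside is unused |
| Months 3–9 | Bracketed exactly by the two unused readings; the 12-month reading lies outside |
| Months 9–15 | Runs 3 months past the last assessment |
| Months 6–12 | Ends at the 12-month reading, but omits the 12-week program and months 3–6 of the continuation; months 6–9 are still within the unstructured phase; the 9-month reading inside is unused |

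No window satisfies the whole paragraph. Months 6–12 comes closest.

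**2. Effect of leaving out the 3- and 9-month readings.** The documents give no utility changes, so those below are assumptions. Each is a mean change from baseline at 3, 9 and 12 months, with straight lines between readings and baseline utility carried forward as comparator. Write them g3, g9 and g12, with time in years.

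- Four readings: 0.25 × (0 + g3)/2 + 0.50 × (g3 + g9)/2 + 0.25 × (g9 + g12)/2
- Two readings: 1 × (0 + g12)/2

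Fading gain (+0.05, +0.02, +0.01):
- Four: 0.25 × 0.025 + 0.50 × 0.035 + 0.25 × 0.015 = 0.00625 + 0.0175 + 0.00375 = 0.0275
- Two: 0.01/2 = 0.005
- Ratio: 0.0275/0.005 = 5.5, so two readings understate the gain

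Gain held from month 3 (+0.03 throughout):
- Four: 0.25 × 0.015 + 0.75 × 0.03 = 0.00375 + 0.0225 = 0.02625
- Two: 0.03/2 = 0.015
- Ratio: 1.75, again understated

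Late gain (0, +0.02, +0.05):
- Four: 0 + 0.50 × 0.01 + 0.25 × 0.035 = 0.005 + 0.00875 = 0.01375
- Two: 0.05/2 = 0.025
- Ratio: 0.01375/0.025 = 0.55, so two readings overstate the gain

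**3. The same courses if the target is months 6–12**, with the 12-month gain applied to the whole half-year:

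- Fading: the month-6 value by interpolation is 0.035. The area is 0.25 × 0.0275 + 0.25 × 0.015 = 0.010625, against 0.5 × 0.01 = 0.005, about 2.1-fold.
- Held: 0.5 × 0.03 = 0.015 either way; no error.
- Late: the month-6 value is 0.01. The area is 0.25 × 0.015 + 0.25 × 0.035 = 0.0125, against 0.5 × 0.05 = 0.025, overstated 2-fold.

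The size of the error therefore depends on both the utility course and the window, and it can go in either direction.

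**The case against.** The best defence is that the horizon means the 6 months before each economic assessment: months −6 to 0 against months 6 to 12. The 12-month contact exists to collect cost and service data, the form is posted together with the EQ-5D-5L, and productivity has the same two anchors as utility. Costs and utility then share an endpoint. It can also be said that an article condenses the full protocol, and that exact dates and interpolation rules often sit in an economic analysis plan.

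Part of this stands. Months 6 to 12 is a coherent window, so it would be wrong to say that no reading brings costs and utilities together. It does, however, omit the supervised program and part of the continuation that the same paragraph says is being valued. As for condensation, the article does more than leave a detail out: it names the two time points for QALYs, and those leave out half of the readings collected.

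A reader might infer more than the text supports:

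- That costs cover 6 months and QALYs 12, so that recurring costs are wrong by about a factor of 2. The horizon is not assigned to costs alone, and the productivity costs share the utility anchors.
- That the before and after windows fall in opposite seasons. This applies to adjacent windows (post window months 0 to 6). Months −6 to 0 and 6 to 12 are a year apart and match by season.
- That the 3- and 9-month EQ-5D-5L data are thrown away. They are left out of the QALY model only; the Statistical analysis section still analyses health outcomes over the follow-up visits.

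**Conclusion.** The point holds in this form: the 6-month windows are undated and not reconciled with utilities 12 months apart, and the QALY model leaves out two of the four EQ-5D-5L readings. In the illustrations, over 0 to 12 months, the four-reading gain ranges from 0.55 to 5.5 times the two-reading gain. For a fixed cost difference, the cost per QALY moves by the same factor in reverse. These sizes rest on assumed utility changes, linear interpolation and a 12-month target. They show what could happen and do not predict the trial's result. The schedule is taken from the text, since Table 1 and Fig. 1 are not shown.

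Severity is moderate. The economic evaluation is secondary, and the CHAMPS outcome and its 9-month comparison are not touched.

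**What to change.** State one dated window, baseline to 12 months, for both costs and QALYs, and include the costs of delivering the program. Give the comparator the same length: either 12 months of Medicare and Pharmaceutical Benefits Scheme extraction before baseline or, for self-reported items, 6-month pre-period costs annualised, with that assumption stated. Compute QALYs as area under the curve from EQ-5D-5L at 0, 3, 9 and 12 months, against baseline utility carried forward over the year.

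The cost is rewording and a little more analysis; the EQ-5D-5L readings are already planned. The downsides are small: a longer database extraction or an annualisation assumption, and a stated rule for extrapolating productivity across follow-up, because it is measured only at baseline and 12 months. For the same reason, a window of months 3 to 9 would be well supported for utility but would have no productivity reading at either end.

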### Design and setting

This study is a multi-site prospective study with a pre and post intervention design with 12 months follow up. Participants will undergo a 12 week structured supervised physical activity program using outdoor exercise park equipment followed by 6 months unstructured physical activity program, including ongoing unsupervised access to the exercise park. Each exercise session will be followed by a social gathering with morning/afternoon tea. Participants will be assessed at baseline and at several follow up time points (3, 9 and 12 months) as detailed in Fig. 1.

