### Study population

#### Inclusion criteria

Older people will be included in the study if they:are aged 60 years and over living in the community (e.g. not living in an institution, such as a nursing home).have had one or more falls in the previous 12 months or are concerned about having a fall.are generally independent around the house (able to take care of themselves) and in the community (e.g. able to walk away from home to visit local stores, friends, and other local venues) and who are able to attend the outdoor exercise park.do not use a walking aid (such as walking frames) or use only a single point stick used for outdoor walking;do not have cognitive impairment (Abbreviated Mental Test Score > 7/10).

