### Sample size calculation

The power calculation is based on increasing physical activity level (CHAMPS) by the end of the 9 month follow-up period. A previous study using the CHAMPS reported mean differences of 687 (SD difference 1509) and 487 (SD difference 1196) energy (calories) expenditure per week in all activities and in moderate intensity activities respectively following 6 months physical activity program for older people [15, 36]. To account for any potential variation between the ENJOY exercise park program and the latter reported community physical activities as well as potential variation in the sample population (people from different multicultural backgrounds) [37] a reduction of 20–25% (500 and 400 cal/week in all activities and in moderate intensity activities respectively) was applied to these outcomes. Using this conservative approach, an effect size d = 0.33, 90% power and alpha =0.05,a sample size of 98 participants is required (G*Power, two tail). To account for potential 15% drop out, a sample of 113 will be recruited. As such, we aim to recruit a sample of 37–38 participants in each participating site.

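### The only cost comparator, the 6 months before the intervention, lies inside the 12-month window used to select fallers, so the cost per QALY can look too favourable if fallers are over-represented

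*Protocol article*

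**What the plan says.** The protocol article (Design and setting) describes a "multi-site prospective study with a pre and post intervention design with 12 months follow up", with one group and no concurrent control. Under Inclusion criteria, people qualify if they "have had one or more falls in the previous 12 months or are concerned about having a fall". These are two alternative routes, and the expected split between them is not given.

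The Economic analysis section sets the cost comparison "over a 6 month pre intervention vs 6 month post intervention time-horizon". It then gives the result a causal reading: "This analysis will estimate the cost per quality adjusted life year gained from providing the Senior Exercise Park intervention and supervised exercise program".

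Several of the costs counted can rise after a fall. For primary care and medicines, "Health care costs will be measured using Medicare and Pharmaceutical Benefits Scheme database extractions". For hospital use, "Hospitalisations measured using participant self-report of diagnosis and days spent in hospital will be converted to a cost". Home nursing, allied health and community services are self-reported, and productivity is collected by questionnaire. Falls history is recorded at baseline, but prospective falls data start only at entry: "Monthly falls calendars will be collected from baseline for 12 months".

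The section names no other comparator and does not mention regression to the mean.

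**The concern.** The baseline period for cost overlaps the period on which people are selected. Provided the programme starts soon after baseline, the 6 months before it fall wholly or almost wholly within the 12-month look-back. A person admitted because of a recent fall has, by construction, at least one fall in that look-back, so the comparator carries more falls than that person's usual rate would give. After entry the count drifts back to the usual rate whatever the programme does, and the costs tied to falls go with it.

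In an uncontrolled comparison this drift cannot be told apart from a programme effect. A spurious saving lowers the incremental cost and, for a given QALY gain, the cost per QALY. The Discussion names local councils and community organisations as the bodies that need this evidence to decide on installing parks.

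**Working it through.** **The plan's own figures.** The article gives no figure for this point. Its only calculation is the sample size for physical activity, which reproduces (paired t-test, d = 500/1509 = 0.331, n = 98, power 0.901) and plays no part here.

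**Assumptions, none from the article.** Annual falls are gamma-Poisson with mean μ and shape k (k = ∞ is plain Poisson). Each person's rate is stable over time and the programme effect is zero. A share f of entrants had a fall in the prior 12 months. The other entrants had none and carry the average rate of non-fallers.

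**Formulas.**
- Probability of no fall in 12 months: p0 = (k/(k+μ))^k, or e^(−μ) for Poisson.
- Expected annual rate of non-fallers: λ0 = μk/(k+μ), or μ for Poisson.
- Expected annual rate of fallers: λ1 = (μ − p0·λ0)/(1 − p0).
- Mean falls in the 6 months before entry: f·(μ/2)/(1 − p0).
- Mean falls in 6 months after entry: [f·λ1 + (1 − f)·λ0]/2.

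**One case in full (μ = 0.5, k = 1, f = 0.6).** p0 = 0.6667, λ0 = 0.3333, and λ1 = (0.5 − 0.2222)/0.3333 = 0.8333. Before: 0.6 × 0.25/0.3333 = 0.450. After: (0.6 × 0.8333 + 0.4 × 0.3333)/2 = 0.317. Change: 0.317/0.450 − 1 = −29.6%.

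**Change in 6-month falls with zero programme effect:**

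| μ | k | natural share of fallers (1 − p0) | f = 0.4 | f = 0.6 | f = 0.7 |
|---|---|---|---|---|---|
| 0.4 | 1 | 29% | −20.4% | −37.4% | −42.3% |
| 0.4 | 2 | 31% | −19.7% | −40.9% | −47.0% |
| 0.4 | ∞ | 33% | −17.6% | −45.1% | −52.9% |
| 0.5 | 1 | 33% | −11.1% | −29.6% | −34.9% |
| 0.5 | 2 | 36% | −8.0% | −32.0% | −38.9% |
| 0.5 | ∞ | 39% | −1.6% | −34.4% | −43.8% |
| 0.7 | 1 | 41% | +1.7% | −18.5% | −24.2% |
| 0.7 | 2 | 45% | +9.5% | −18.4% | −26.3% |
| 0.7 | ∞ | 50% | +25.9% | −16.1% | −28.1% |

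When f equals the natural share the change is exactly 0. Above it, falls drop; below it, they rise.

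**Sensitivity to the concern-only entrants (f = 0.6, k = 1; μ = 0.4, 0.5, 0.7).** With non-fallers' average rate the changes are −37.4%, −29.6% and −18.5%. If these entrants have the population-average rate, they are −32.0%, −22.2% and −7.2%. If they have the fallers' rate, they are −18.4%, −7.4% and +9.0%.

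**From falls to cost.** If a share s of pre-period cost is fall-related and the rest is unchanged, total cost changes by s times the change in falls. Take μ = 0.6, k = 1 and s from 5% to 40%, again assumed. If all entrants are fallers, falls change by −39% and total cost by −2.0% to −15.6%. At f = 0.75 total cost changes by −1.6% to −12.5%, and at f = 0.5 by −0.8% to −6.2%.

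**Does an earlier reference period help?** Simulating μ = 0.5, k = 1, f = 0.6 gives 0.317 mean falls in a 6-month window ending before the look-back and 0.317 after entry, against 0.450 in the planned window. Under stable rates and no effect, the earlier window removes the artefact.

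**The case against.** A reader might infer that the cost per QALY will be biased in favour of the park, and that 16% to 53% is the size of that bias. The documents support neither.

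- **Direction.** Entry is by a fall or by concern, with no split given. The 60% and 70% shares are assumptions above the natural share. At 40% and 0.7 falls per year the same model gives a rise of 2% to 26%. Concern-only entrants may also have a higher fall risk than other non-fallers, which shrinks the drop. The largest drops come from plain Poisson, where everyone has the same risk. All of this stands.
- **Size.** The percentages are falls, not costs. Without the fall-related share of cost, no cost bias can be stated. This stands.
- **Opposing selection.** Entrants must be independent, mobile and free of medical contraindication. Someone still disabled by a costly fall is screened out at entry but can have such a fall later, which pushes costs up after entry. Ageing and general cost growth work the same way. These offsets are real and of unknown size, and without a control group none can be separated from a programme effect.
- **Scope.** The uncontrolled design is declared, the economic analysis is not the primary outcome, and an article may leave subgroup and sensitivity analyses to fuller documents. That is fair for detail. It does not answer the point, because the article itself fixes the comparator and the causal reading of the ratio.

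**Conclusion.** The concern holds in conditional form. Selection is partly on a recent fall, the comparator lies inside the selection window, there is no control group, and the costs counted can respond to falls. If fallers are over-represented among entrants, part of any saving can be regression to the mean. If they enter at their natural share (29% to 50% under these assumptions) the artefact is zero, and below that it reverses.

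The 16% to 53% drop in 6-month falls rests on 0.4 to 0.7 falls per year, a 60% to 70% faller share, stable individual rates and concern-only entrants who resemble other non-fallers. Only the fall-related part of cost is affected, and its size in money or per QALY cannot be derived from the protocol. The point concerns a secondary analysis and is worth acting on because a partial remedy is cheap.

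**What to change.** In the Economic analysis section:

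1. Extend the planned Medicare and Pharmaceutical Benefits extraction back to a 6-month reference period that ends before the 12-month selection window (18 to 12 months before baseline), and pre-specify a sensitivity analysis of database costs against that period.
2. Report the pre-post cost change by prior-fall status as a descriptive check only. Falls history is already collected. The split conditions on the selection variable, so it shows regression to the mean without correcting it, and the groups will be small with 113 recruited.
3. State that the pre-post saving may include regression to the mean.

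Two tempting alternatives should be avoided. Removing the qualifying fall's costs from the pre-period alone would build in the opposite bias, and no described data source ties pre-baseline costs to a particular fall. Labelling the unadjusted ratio a best case would presuppose the direction.

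The cost is a longer date range in an extraction already planned, which the data consent must cover, plus analysis wording. The change does not correct self-reported hospital, home nursing and allied health use or productivity costs, and the earlier window relies on fall rates being stable over time.
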